### Data management {19}

The research team will frequently monitor the completion of survey data for completeness and send reminders to participants to amend incomplete data. The interview will be audio recorded, automatically transcribed using Microsoft Teams, and manually edited to remove identifying information. Transcripts will be sent to participants for approval (member checks). The audio file will be destroyed after the transcription has been approved.

### Confidentiality {27}

This study will be conducted according to the Declaration of Helsinki version 2013 principles and following the Good Clinical Practice (GCP) guidelines promulgated by the International Conference on Harmonization (ICH). The handling of personal data will comply with the General Data Protection Regulation 2018 (GDPR), in Dutch, the “Algemene verordening gegevensbescherming” (AVG).

The researcher will give each participant a unique identification code. Participant contact details and linking identification codes will be saved in a password-protected file and stored separately from the data. The data will be stored following RadboudUMC protocols. The analysis, when necessary for data protection, will be conducted in a secure Digital Research Environment (DRE). Data will not be published; however, further researchers can request access after signing a data-access agreement. The principal investigator will destroy documents containing personal information, such as consent forms or non-anonymised data, after 15 years.

### Plans for collection, laboratory evaluation and storage of biological specimens for genetic or molecular analysis in this trial/future use {33}

No biological specimens will be collected.

## Statistical methods

### Statistical methods for primary and secondary outcomes {20a}

The main analysis will be conducted in two stages. The first is according to the intention-to-treat (ITT) analysis principle [60], with all participants included where possible. This includes dropouts and non-completers of the programmes. Second, we will repeat the analysis Per-Protocol (PP) [60] to gain a clearer picture of the intervention-related effects, excluding non-completers or poor-quality data (see exclusions below). To evaluate whether there are differences between the conditions at the post-test, considering baseline differences, a series of ANCOVAs with the condition as the IV and the post-test as the DV, with baseline scores, sex, and age as covariates will be run on primary and secondary outcomes. To evaluate the long-term effects of the intervention and the control condition, linear mixed models (LMM) will be fitted to predict each outcome variable. The same approach will be applied to evaluate the tertiary outcomes.

For more details, see our pre-registration: osf.io/q8c6u.

### Interim analyses {21b}

No Interim analyses will be done.

### Methods for additional analyses (e.g. subgroup analyses) {20b}

To understand the pattern of an individual response, we will calculate the Reliable Change Index (RCI) for pre-post change scores, expecting more individuals in the intervention condition to reliably improve on primary, secondary, and tertiary outcomes than in the control condition [61]. Furthermore, factors including adherence, expectancy and credibility, past art experience and personality will be compared between groups. If the groups differ significantly on any scale, we will include that scale as an exploratory covariate.

Finally, we will assess any differential effect of the intervention on highly sensitive individuals in three ways. First, we expect SPS to predict a greater likelihood of improvement in the RCI analyses. Second, moderation analysis will be used to assess whether individuals with higher scores on SPS experience larger increases in primary and secondary outcomes from the intervention. Third, qualitative sub-group analysis will be used to investigate mechanisms, barriers and facilitators for a high SPS subgroup, by comparing their responses to a group of low and moderate SPS individuals.

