### Expectation, credibility, adherence, and enjoyment

To understand how participants’ expectations and adherence might impact the results of the trial, several aspects will be assessed at time point 1. Expectation and credibility will be measured through the Credibility and Expectancy Questionnaire (CEQ), which has six questions about how much participants expect the programme to benefit their well-being [56]. We have slightly modified this questionnaire from its intended use as a clinical instrument for therapies, asking about improvement in functioning by replacing the term “functioning” with “well-being” in the questions.

To measure adherence, as part of the programme, each day, participants will also be asked to indicate whether they fully, partially or did not complete the programme elements for that day. These questions were introduced in the enrollment meeting with emphasis on the need for honesty that would not impact any compensation. Adherence will also be monitored via the number of sign-ins and their progress in the online programmes. Finally, enjoyment of the programmes will be assessed on a 1–7 Likert scale.

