### Participant timeline {13}

#### Enrollment and baseline

In an enrollment meeting hosted on Microsoft Teams, the researcher will walk the participant through the selected programme components and instructions with a PowerPoint presentation and provide time for questions. As listed in the information sheet, advertisement, and screening survey, the participants will be asked for their postal address so that the login details for the respective programme and the free museum tickets (intervention only) can be sent via post. Participants will set up an account on the Samply Research Application [58] to receive reminders about the study. At the end of the meeting, the researcher will explain that the surveys will be sent to them via email (via Castor). Once the participant has no further questions, the enrollment meeting will finish. The participants will then be sent the baseline survey. The list of baseline questions is provided in the overview in Table 3.

**Table 3 Tab3:** Outcomes and timepoints of assessment

Assessment tools	Baseline T1	Post T2	Follow-up T3

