### Implementation {16c}

The enrollment researchers will assign participants to conditions during the enrollment meeting, after informed consent, using the automatic randomisation sequence generated by Castor.

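### The test-then-adjust rule for exploratory covariates takes in adherence and expectancy, both recorded after allocation, so the adjusted effect it yields does not in general estimate the effect of assignment

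*Protocol article*

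**What the plan says.** The rule is in the protocol article under Methods for additional analyses {20b}. It first says that "factors including adherence, expectancy and credibility, past art experience and personality will be compared between groups", and then: "If the groups differ significantly on any scale, we will include that scale as an exploratory covariate".

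The timing of the listed measures has to be put together from other sections.

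- **Adherence.** Under Expectation, credibility, adherence, and enjoyment, "each day, participants will also be asked to indicate whether they fully, partially or did not complete the programme elements for that day". Sign-ins and progress in the online programme are tracked as well, and Table 3 lists the adherence item at the post-test.
- **Expectancy and credibility (CEQ).** The same section opens by saying that "several aspects will be assessed at time point 1", and Table 3 places the CEQ at T1. It describes the CEQ as a questionnaire "which has six questions about how much participants expect the programme to benefit their well-being".
- **Allocation.** Under Implementation {16c}, "The enrollment researchers will assign participants to conditions during the enrollment meeting, after informed consent".
- **Briefing and survey.** Under Enrollment and baseline, in that same meeting "the researcher will walk the participant through the selected programme components and instructions with a PowerPoint presentation". After the meeting closes: "The participants will then be sent the baseline survey".
- **Past art experience and openness.** Both are in the T1 survey (Demographics and individual differences; Table 3). Openness is the only Big Five measure collected, so it is read here as the personality scale.

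The main ANCOVA in {20a} has a fixed covariate set: the baseline score, sex and age.

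**The concern.** Adjusting a randomised comparison is safe when the covariate cannot have been changed by allocation. Adherence fails that condition, because it is a response to the programme that was assigned. The CEQ fails it too, because participants answer it about a programme they have just been allocated to and shown, by a researcher who knows the arm (Who will be blinded {17a}).

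If allocation moves one of these scales, a significant arm difference becomes more likely, and that difference is what brings the scale into the model. Adjustment then removes any part of the effect that runs through the scale. It can also introduce bias through unmeasured causes that the scale shares with the outcome, such as general motivation. The coefficient for condition is then no longer the total effect of assignment.

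The trait scales raise a lesser problem. Allocation is unlikely to move them, so an arm difference is essentially chance. Testing for it tells us nothing about whether the scale is prognostic, yet it decides which model is fitted.

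At stake is the interpretation of an exploratory result. If the arms differ on expectancy, a reader may take the adjusted estimate as showing whether the effect survives expectancy. That matters because the Discussion presents minimised expectancy effects as a strength of the design.

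**Working it through.** The plan attaches no figure to this rule, so there is none to reproduce. The check covers the order of events, then the size of the shift, then chance selection.

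**1. Order of events.** Consent, then allocation, then explanation of the assigned programme, then the T1 survey (with CEQ, openness and arts experience), then the programme (with daily adherence), then the post-test. Every scale under the rule is therefore recorded after allocation. For adherence and the CEQ, the content of the measure also refers to the assigned programme. Openness and past art experience describe the person and are unlikely to change because of a briefing.

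**2. Size of the shift.** In a linear model, adding a scale with arm difference *a* (in SD) and within-arm outcome slope *s* moves the treatment coefficient by −*a* × *s*. The documents give neither value, so both are assumed.

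- *a* = 0.4, *s* = 0.1: 0.4 × 0.1 = 0.04 SD, which is 0.04 / 0.35 = 11% of the planned effect.
- *a* = 0.4, *s* = 0.3: 0.4 × 0.3 = 0.12 SD, or 34%.
- *a* = 0.4, *s* = 0.4: 0.4 × 0.4 = 0.16 SD, or 46%.

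With *a* and *s* of the same sign the estimate falls; with opposite signs it rises.

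**3. How often the rule adds the scale, and what follows.** A simulation used 3,000 trials per setting, 49 per arm and a pre-post correlation of 0.72 (both taken as stated in Sample size {14}), and a true total effect of 0.35. Two mechanisms were assumed. In the first, the scale mediates the effect with slope 0.2 or 0.3. In the second, it has no effect of its own but correlates 0.5 with an unmeasured cause whose effect on the outcome is 0.3, giving an implied slope of 0.5 × 0.3 = 0.15.

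| Arm difference *a* | Scale added in about | Adjusted mean, mediator slope 0.2 | Adjusted mean, mediator slope 0.3 | Adjusted mean, shared cause only |
|---|---|---|---|---|
| 0.3 | 31% | 0.29 | 0.26 | 0.30 |
| 0.5 | 68% | 0.25 | 0.20 | 0.28 |
| 0.8 | 97% | 0.19 | 0.11 | 0.23 |

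These agree with 0.35 − *a* × *s*; for example, 0.35 − 0.5 × 0.3 = 0.20. Adjusting for the baseline score alone gave means of 0.346 to 0.353.

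With no true effect and the shared cause only, the adjusted estimate averaged −0.04, −0.07 and −0.12 for the three values of *a*. Rejection at a nominal 5% was 6.1%, 8.1% and 11.3% when the scale was always included, and 4.6%, 7.4% and 11.1% when it was included only if the arms differed significantly. The baseline-only model rejected in 4% to 5%.

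**4. Chance selection.** If no scale truly differs by arm and the tests are independent at 5%, the probability of adding at least one is:

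- four scales, as listed: 1 − 0.95⁴ = 18.5%;
- five, counting expectancy and credibility separately: 1 − 0.95⁵ = 22.6%, about 23%;
- the two trait scales alone: 1 − 0.95² = 9.75%.

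This is the chance that the model changes. It is not a bias.

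**The case against.** The strongest reply is that the rule sits among the additional analyses and calls the added scale exploratory, while the main ANCOVA has covariates fixed in advance. That stands. A reader might infer that the primary estimate is biased, or that the adjusted effect will be presented next to the primary result. The document supports neither: it does not say which model receives the covariate or how the result will be reported. The pre-registration to which it refers for analysis details may settle this and is not shown here.

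A reader might also infer that the rule operates only when adjustment does harm. That is too strong. Adjusting for openness or past art experience after a chance imbalance does not bias the effect. They are collected in the same post-allocation survey as the CEQ, but they are traits that allocation is unlikely to move.

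It can further be said that these measures are collected to understand how expectation and adherence bear on the results, which is a legitimate exploratory question. It is, but it is a mediation-type question. It needs the assumption that the scale and the outcome share no unmeasured cause, and its answer is not the effect of assignment. The exploratory label does not supply that assumption.

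Finally, the shift may be small. The pilot judged the programmes comparable in intensity, credibility and enjoyment. It had three participants per condition, so it is weak evidence, but nothing in the documents shows a large arm difference. The bias figures are assumed throughout.

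**Conclusion.** The concern holds for the exploratory adjusted analyses. Followed as written, the rule can place adherence or the CEQ in the model, is most likely to do so when allocation has shifted them, and then gives a coefficient that does not in general estimate the total effect of assignment. The ANCOVA with fixed covariates is not affected by this rule. For openness and past art experience the fault is data-dependent selection only.

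Size and direction rest on assumptions. With a 0.4 SD arm difference and slopes of 0.1 to 0.4, the shift is 0.04 to 0.16 SD against a planned 0.35. It is zero if either the true arm difference or the slope is zero, and it reverses if they have opposite signs. The 18.5% chance of at least one addition assumes four independent scales with no true arm difference. The point is secondary, but it should be corrected because the rule is explicit and easily changed.

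**What to change.** - Delete the significance trigger in {20b}.
- Name openness and past art experience in advance as covariates in one sensitivity ANCOVA, fitted whatever balance is observed. First settle the direction of the two arts items: as described, a score of 7 means high interest on one and no attendance in the past year on the other, and the article mentions no reversal before they are summed.
- Report adherence and the CEQ descriptively by arm. Do not present any model adjusted for them as a treatment effect. If such a model is kept, label it an exploratory mediation-type analysis and state its assumption about unmeasured common causes.
- Add that the per-protocol analysis in {20c} also selects participants on post-allocation adherence (sign-ins and activities completed), so it needs the same caution and does not solve the problem.

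The cost is a sentence or two in the analysis plan and no new data. The trial gives up a simple statement that the effect does or does not survive adjustment for expectancy, which the planned model could not properly support.

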One potential avenue that could support young adults’ well-being, including highly sensitive young adults, is the practice of beauty appreciation. Large-scale cross-sectional studies suggest that trait appreciation of beauty may be a protective factor associated with well-being [15–19]. As reviewed by [name] et al. [20], individuals with a higher appreciation of beauty, aesthetic sensitivity, or art-savouring, or a tendency to experience awe exhibit elevated subjective well-being [17, 21], greater life satisfaction [16], reduced depression [22], and improved physical health [15]. Lee et al. [15] also demonstrated predictive validity after accounting for other personality traits, like openness to experience. Notably, aesthetic sensitivity, representing an awareness and appreciation of the environment, is a fundamental part of SPS and those who are more sensitive experience more beauty and awe from the world around them [23]. Many studies suggest that of the facets of the Highly Sensitive Person Scale used to measure SPS [18], aesthetic sensitivity tends to be associated with positive health and well-being outcomes much more than other facets [24]. The past evidence indicates that cultivating an appreciation for beauty could be beneficial for young adults generally, and possibly especially so for young adults with heightened sensitivity.

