### Main hypothesis

H1: The intervention condition will report larger increases in the primary outcome, appreciation of beauty, compared to the control group at the post-test.

H2: The intervention condition will report a larger decrease in the secondary outcome, psychological distress and a larger increase in mental well-being, compared to the control group at the post-test.

H3: The intervention condition will report higher levels of the primary outcome, appreciation of beauty, secondary outcomes: mental well-being, alongside lower levels of psychological distress compared to the control group at follow-up.

Exploratory H4: Sensory processing sensitivity will moderate improvements in both the primary and secondary outcomes.

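### One of the three planned checks of differential benefit by sensory processing sensitivity has no condition contrast, so as worded it can show only prognosis

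*Protocol article*

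**What the plan says.** Under Methods for additional analyses {20b}, the RCI is introduced as a comparison of the two arms, "expecting more individuals in the intervention condition to reliably improve on primary, secondary, and tertiary outcomes than in the control condition". SPS plays no part in that sentence.

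The next paragraph turns to SPS and states its purpose: "we will assess any differential effect of the intervention on highly sensitive individuals in three ways". Three strands follow:

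- A first strand: "we expect SPS to predict a greater likelihood of improvement in the RCI analyses".
- A second, separate strand: "moderation analysis will be used to assess whether individuals with higher scores on SPS experience larger increases in primary and secondary outcomes from the intervention".
- A third strand, a qualitative comparison of high-SPS participants with low- and moderate-SPS participants.

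The hypothesis served is H4 (Main hypothesis), which is labelled exploratory and worded as moderation: "Sensory processing sensitivity will moderate improvements in both the primary and secondary outcomes". The Trial design section {8} says that the qualitative subgroup work together with the moderation analysis will settle whether high-SPS people gain most. It does not mention the RCI.

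**The concern.** A differential effect means that the intervention-minus-control difference changes with SPS. The first strand asks something else: whether people with higher SPS are more likely to improve. That can be true to the same extent in both arms, in which case SPS is prognostic and the treatment effect is constant.

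The neighbouring sentences show that the article names the comparison when it means one. The arm comparison of improvers names both conditions, and the second strand speaks of moderation and of gains from the intervention. The first strand does neither. Since moderation is listed separately as the second way, the natural reading is that the first is not a moderation test.

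At stake is how a mixed result would be read. If the moderation test is null, which is quite possible because the sample size was set for the primary ANCOVA, and SPS nevertheless predicts reliable improvement, the text as it stands lets that association be offered as evidence that highly sensitive people benefit more.

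**Working it through.** The article states no figure for this analysis, so there is none to reproduce. The check asks how often the first strand would come out positive when the true condition by SPS interaction is zero.

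**Inputs from Sample size {14}, taken as printed.** Effect d = 0.35; pre-post correlation r = 0.72; alpha 0.05; 49 analysable per group, so 2 × 49 = 98.

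**Assumed inputs, not in the article.** SPS is standardised, with a slope b on the post score beyond baseline of 0, 0.1, 0.2 or 0.3 SD per SD, the same in both arms. The reliability used in the RCI is 0.72 (the printed retest value) or 0.90 (an assumption, to show the range).

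**Model.** post = 0.72 × pre + 0.35 × arm + b × SPS + error, with no arm × SPS term. The expected arm difference is 0.35 at every SPS level, while the SPS slope is b within each arm. Any positive SPS finding is therefore prognosis by construction.

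**RCI rule.** Improved if change > 1.96 × √(2 × (1 − reliability)).

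- Reliability 0.72: 1.96 × √0.56 = 1.47 SD.
- Reliability 0.90: 1.96 × √0.20 = 0.88 SD.

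**Expected improvers at reliability 0.72, b = 0.** The SD of change is √(2 × (1 − 0.72)) = 0.748. In control, P(Z > 1.467/0.748 = 1.96) = 2.5%, or 49 × 0.025 ≈ 1.2 people. In the intervention arm, P(Z > (1.467 − 0.35)/0.748 = 1.49) = 6.8%, or 49 × 0.068 ≈ 3.3 people. That is about 4.5 improvers among 98.

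**Results.** Logistic models for improvement, likelihood-ratio tests, true interaction zero:

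| Test | RCI reliability | b = 0.1 | b = 0.2 | b = 0.3 |
|---|---|---|---|---|
| SPS predicts improvement | 0.72 | about 9% | about 24% | about 44% |
| SPS predicts improvement | 0.90 | about 16% | about 41% | about 74% |
| Condition × SPS | either | 4–6% | 4–6% | 4–6% |

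Reruns with other seeds, and with Wald in place of likelihood-ratio tests, gave 6–12%, 19–26% and 41–50% at reliability 0.72, and 15–16%, 41–43% and 73–76% at 0.90. The interaction test ranged from 1–2% (Wald, which is conservative at such sparse counts) to 8%.

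**Where there is no inflation.** With b = 0, the SPS test is not inflated. The same holds if SPS relates only to level. When SPS correlates ρ with both pre and post (each with SD 1), its covariance with change is ρ − ρ = 0. Simulation with ρ = 0.3 and 0.5 gave significance in 5–6% of fitted trials at both reliabilities.

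**Reading the strand within the intervention arm only.** This does not help, because there is still no control contrast. At 49 per arm (Wald), SPS was significantly favourable in about 3%, 10% and 20% of trials for b = 0.1, 0.2 and 0.3. At 57 per arm the rates were about 4%, 14% and 27%.

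**Stability.** At reliability 0.72, about 22–34% of simulated trials could not be fitted by ordinary logistic regression, because there were only about 4 to 6 improvers, 1 to 2 of them controls. The rates in that row are conditional on fitting and are approximate.

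**The case against.** The strongest reply has four parts.

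**The sentence is an expectation, not a model.** It follows a stated interest in differential effects, and the RCI analyses were introduced as an arm comparison. The article also refers the reader to a pre-registration, not shown here, which may contain the interaction. This stands as a limit on certainty: one cannot say that the investigators will fit only a main effect. It does not rescue the printed criterion, which answers a different question from the one it is listed under and sits beside a separately listed moderation analysis.

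**The right test is already planned.** This is correct for the primary and secondary outcomes on their continuous scales, and it is why the point stays small. It does not cover the RCI outcome.

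**The trial's conclusion about SPS does not rest on the RCI.** This also stands. A reader might infer that one of three pillars of the headline SPS claim is unsound. But Trial design {8} rests that claim on moderation plus qualitative work, H4 is exploratory, and no rule lets the RCI result decide alone.

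**A prognostic effect on change is not shown.** A reader might infer from the Background that such an effect is likely, since SPS is tied there to more psychological problems and "those who are more sensitive experience more beauty and awe from the world around them". Those statements concern levels. The RCI uses change, and an equal association with pre and post scores implies none with change. The article gives neither the size nor the sign of an SPS effect on change.

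**Conclusion.** The point holds in a limited form. As worded, the first strand is an association of SPS with improvement and cannot separate prognosis from effect modification. That follows from the wording and needs no simulation.

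The size of the risk is conditional. It is nil if SPS has no effect on change beyond baseline, and roughly 10% to 75% false support for assumed slopes of 0.1 to 0.3 SD, depending on the RCI reliability (0.72 or an assumed 0.90). The slopes and the 0.90 are assumptions. The documents do not support saying that false support is likely, only that the criterion gives no protection against it.

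The primary and secondary conclusions are untouched, and so is the planned moderation analysis. The correction is worth making because it is cheap and prevents a predictable misreading.

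**What to change.** Replace the first strand with wording such as: *Differential benefit by SPS will be judged only from the condition by SPS interaction, in the planned moderation analysis of the continuous primary and secondary outcomes. Where enough participants reliably improve, the same interaction (SPS continuous and centred) will be estimated in the RCI model, by a penalised or exact method if counts are sparse, and reported with a confidence interval as exploratory. Any association of SPS with reliable improvement that lacks this contrast will be described as prognostic.*

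If the pre-registration already specifies the interaction, aligning the sentence with it is enough.

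The cost is a few lines of text and one model term, with no new data. The downside is that the RCI interaction will have very low power and, with only a handful of improvers, may not be estimable by ordinary logistic regression. In that case the moderation analysis carries the quantitative question, and the RCI result by SPS is description only.
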